### Study endpoints

Primary endpoint is the number of futile high dose ^131^I treatments that could have been avoided by implementation of pre-therapy imaging based on post-therapy scintigraphy

Four secondary endpoints were defined: (1) Synchronized QA/QC of ^124^I PET in the Netherlands, (2) correlation of ^124^I PET/CT and ^18^F-FDG PET/CT with histopathological parameters, (3) correlation between ^124^I PET/CT findings during rhTSH and withdrawal combined with low-iodine diet and (4) correlation between ^124^I PET/CT and ^131^I-scintigraphy dosimetry.

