## Methods and design

### Study objectives

The primary aim of the study is to evaluate the value of combined imaging with ^124^I and ^18^F-FDG PET/CT in the prevention of futile treatment with high therapeutic activity of ^131^I. Interpretation of both PET-scans will lead to a positive or negative treatment proposal. This will be compared with the actual response on therapy. The definition of a futile treatment will be a negative post blind ^131^I therapy scintigraphy.

We define four secondary aims. Firstly, our aim is to organize a synchronized introduction and QA/QC of ^124^I PET/CT in the Netherlands. More specifically, we aimed to create a procedure for the cross-calibration of ^124^I PET/CT in a multicenter setting, which guarantees reliable and comparable quantification, and is practical to use. The procedure should result in calibration factors per scanner and an indication of a measurement threshold of the scanner, which is defined as the lowest activity that can be reliably quantified. The measurement threshold will be determined per vendor.

Secondly, translational correlation of ^124^I and ^18^F-FDG PET/CT with histopathology (where available) and treatment outcome will be done, in an explorative setting. The outcome of the treatment is defined as a positive or negative post-therapy scan. This scan and both ^124^I and ^18^F-FDG PET/CT will be correlated with histopathological features. The expression of different markers will be quantified in the samples. In this way we aim to determine which histopathological features of both primary tumor and metastatic lesions can predict outcome of the scans.

Thirdly, the study aims to investigate whether ^124^I PET/CT has the same diagnostic, dosimetric and prognostic yield during stimulation with rhTSH as with hormone withdrawal combined with low-iodine diet. Because ^124^I PET/CT will be performed both after stimulation with rhTSH and after withdrawal from levothyroxine it is possible to determine any differences in outcome from the two scan preparation strategies. Both visual assessment as the quantifiable data will be compared. As simultaneous administration of ^131^I and ^124^I is required this can only be done in selected.

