#### Review panel

The local nuclear physician will assess all scans and, additionally, an expert review panel consisting of experienced nuclear physicians will assess every scan and every lesion individually as either positive or negative. Finally, the expert panel will discuss their disagreements to reach consensus on every scan and of every lesion in each scan.

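### Secondary endpoints 3 and 4 are defined as correlations, which cannot answer whether two scan preparations give the same yield or how two dosimetry methods compare

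*Protocol article*

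**What the plan says.** The Study endpoints section of the protocol article lists, as its last two secondary endpoints, "3) correlation between ^124^I PET/CT findings during rhTSH and withdrawal combined with low-iodine diet and (4) correlation between ^124^I PET/CT and ^131^I-scintigraphy dosimetry".

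The Study objectives section frames the matching aims differently. For the third aim it asks "whether ^124^I PET/CT has the same diagnostic, dosimetric and prognostic yield during stimulation with rhTSH as with hormone withdrawal". It adds that, because some patients are scanned under both preparations, "it is possible to determine any differences in outcome from the two scan preparation strategies", and that "Both visual assessment as the quantifiable data will be compared". For the fourth aim it says that 124I PET is not the gold standard for dosimetry and that its results will therefore be compared with 131I-scintigraphy dosimetry and related to clinical outcome.

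The Statistical analysis section names chi-square and trend tests for the reduction in futile treatments, accuracy measures, and logistic regression where appropriate. It names no paired or agreement method for endpoints 3 and 4. The Review panel section says that the expert panel "will assess every scan and every lesion individually as either positive or negative", so visual results will exist at both scan and lesion level.

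**The concern.** Whether two preparations have the same yield is a question about differences within pairs. Correlation answers another question: whether lesions or patients that rank high on one measurement also rank high on the other. If one preparation gave half the lesion dose of the other throughout, the correlation would be as high as if the doses were equal. For paired positive/negative reads, a clear positive correlation can coexist with one preparation missing lesions that the other shows.

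The protocol itself treats scale as important: its first secondary aim seeks calibration factors per scanner so that quantification is comparable across centres. A correlation endpoint would not show a scale error between the two dosimetry methods.

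Endpoint 3 also helps to interpret the main result. The pre-therapy 124I scan is done under rhTSH, while the post-therapy scintigraphy that serves as reference follows withdrawal. If scans under rhTSH systematically showed less, that could produce negative 124I scans with positive post-therapy scintigraphy. The within-patient comparison of preparations is where the study could see this, and a correlation coefficient would not reveal it.

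**Working it through.** **The plan's own figure.** The document gives no design figure for endpoints 3 and 4. Its only one, in Sample size calculation, concerns the primary endpoint: with 100 evaluable patients and a proportion of 40%, the exact 95% CI extends about 10%. Exact limits for 40 of 100 are 30.3% and 50.3%, that is 9.7 points below and 10.3 above. The figure reproduces, and nothing here alters it.

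**Quantitative data.** Assumed inputs, since the document gives none: true log dose x varies between lesions with SD 1.0, each measurement carries independent log-scale error with SD 0.2, and the dose ratio between the two measurements is f.

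- First measurement: a = x + e1. Second: b = x + ln(f) + e2.
- Var(a) = Var(b) = 1.0² + 0.2² = 1.04. Cov(a, b) = 1.0² = 1.00.
- r = 1.00 / √(1.04 × 1.04) = 1/1.04 = 0.96.

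The constant ln(f) enters neither the variances nor the covariance, so r = 0.96 at f = 1.0 and at f = 0.5.

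The paired log difference b − a has mean ln(f) and SD √2 × 0.2 = 0.283. The 95% limits of agreement on the ratio are f × exp(±1.96 × 0.283):

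- f = 1.0: mean ratio 1.00, limits 0.57 to 1.74.
- f = 0.5: mean ratio 0.50, limits 0.29 to 0.87.

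**Sensitivity to where the error sits.** With the error on one measurement only, r = 1/√1.04 = 0.98 for every f. Lin's concordance coefficient is 2 / (1 + 1.04 + ln(f)²), and the limits are f × exp(±1.96 × 0.2):

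| f | r (log scale) | Lin's coefficient | Mean ratio | 95% limits |
|---|---|---|---|---|
| 1.0 | 0.98 | 0.98 | 1.00 | 0.68 to 1.48 |
| 0.7 | 0.98 | 0.92 | 0.70 | 0.47 to 1.04 |
| 0.5 | 0.98 | 0.79 | 0.50 | 0.34 to 0.74 |

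The level of r depends on the assumed SDs. That it does not move with f does not.

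**Visual reads.** A hypothetical table of 30 independent pairs: 12 positive under both preparations, 8 positive under withdrawal only, 0 under rhTSH only, 10 negative under both.

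- Detection: 12/30 = 40% against 20/30 = 67%, a difference of 27 points.
- Correlation (phi) = (12 × 10 − 0 × 8) / √(12 × 18 × 20 × 10) = 120/207.8 = 0.58.
- Exact McNemar on the 8 discordant pairs, all in one direction: p = 2 × 0.5⁸ = 0.008.

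The correlation is clearly positive although one preparation detects systematically less.

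**The case against.** The strongest reply is that the endpoint wording is shorthand. Study objectives says that differences can be determined and that visual and quantitative data will be compared, and the abstract lists both aims as comparisons. No correlation coefficient is named anywhere, and the article uses the verb correlate loosely, for instance for the phantom study. The choice of agreement statistic may also properly sit in a full protocol or SAP that is not shown.

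Much of this stands. A difference analysis may well be intended, and the absence of limits of agreement or McNemar from an article is not itself a fault. It does not remove the mismatch: Study endpoints is the formal definition, it names correlation for both, and nothing in Statistical analysis corrects it. If a comparison is intended, the endpoint should say so.

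Three stronger readings are tempting but not supported:

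- A reader might infer that the stated chi-square and logistic methods will be run on lesions as if independent. Statistical analysis ties chi-square and trend tests to futile treatments, which are counted per patient, and assigns neither these nor logistic regression to lesion-level data. The panel's lesion reads describe how scans are assessed, not a unit of analysis. Inflation of the type I error cannot be put in numbers either: what matters for paired data is how within-lesion differences cluster by patient, and the document gives nothing on this.
- A reader might infer that endpoint 4 also asks for sameness. Only the third aim says so; the fourth says compare.
- A reader might infer that a high correlation would lead to rhTSH replacing withdrawal. No such rule is stated.

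**Conclusion.** The point holds as a mismatch between endpoint and aim. It is clear for endpoint 3, whose aim is explicitly about sameness and differences. It is weaker for endpoint 4, where agreement is implied by the purpose of comparing two methods. That correlation is blind to a constant shift or scale factor is a mathematical property and needs no assumption. The values 0.96 and 0.98 and the twofold ratio are illustrations on assumed SDs and an assumed bias, and the document says nothing about the true bias.

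Severity is minor to moderate. Both endpoints are secondary, endpoint 3 rests on a subgroup of unstated size, and the primary endpoint and its sample size are untouched.

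**What to change.** Reword endpoints 3 and 4 so that they match the aims:

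- **Quantitative data:** the paired mean log ratio (rhTSH to withdrawal; 124I to 131I dosimetry), back-transformed, with 95% CI and 95% limits of agreement. If a conclusion of sameness is wanted, state the acceptable ratio in advance; its value is for the investigators and can sit in the SAP.
- **Visual reads (endpoint 3):** the paired difference in detection between preparations, with the discordant pairs shown and McNemar's test where there is one pair per patient.
- **Several lesions per patient:** intervals clustered by patient, for example from a mixed model, GEE or a patient-level bootstrap.
- **Correlation:** keep as a descriptive addition.

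The cost is a change of endpoint wording and of analysis code. No new data are needed. Clustered intervals will be slightly wider.

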### Study procedures

The study consists of four phases: pre-therapy, between pre-therapy and therapy, therapy and follow-up phase. For each phase the main study procedures are described below. Figure 2 shows an overview of the most important procedures.

**Figure 2 F2:**
[figure not shown]
**Flow chart THYROPET study.** †Only in selected centers; if allowed according to local radiation safety regulations; *if available in center; ^# 124^I and ^18^F-FDG PET/CT only if pre-therapy scan was positive.

#### Pre-therapy phase

Patients with biochemically confirmed recurrent DTC, will undergo ^18^F-FDG and ^124^I PET/CT imaging after pre-treatment with two injections of rhTSH. ^18^F-FDG will be administered and ^18^F-FDG PET/CT will be performed 60 minutes post injection. Subsequently, 74 megabecquerel (MBq) of ^124^I is administered intravenously. ^124^I PET/CT scans are then performed 24 and 96 hours after administration of ^124^I.

#### Between ‘pre-therapy phase’ and ‘therapy phase’

If either the ^18^F-FDG PET/CT or the ^124^I PET/CT shows metastatic lesions and it is possible to acquire a biopsy from the lesion, this will be done to correlate histopathological characteristics with both the result of the scans and the resection specimen of the original tumor. If multiple metastatic lesions are present on either of the scans, a biopsy will be pursued to acquire from every lesion, but only if the ^124^I or FDG uptake differs between the different lesions. This will be done in easily accessible metastatic lesions without large risks of complications and/or discomfort for the subject.

After the pre-therapy phase, subjects will start thyroid hormone withdrawal 4 weeks prior to ^131^I therapy. A low-iodine diet (LID) will be prescribed one week before the therapy.

#### Therapy phase

Subjects will undergo ^131^I therapy with 7400 MBq of ^131^I orally. In a subgroup of subjects (in selected centers) additional ^124^I PET/CT scans will be performed for dosimetric evaluation. Furthermore, the influence of the method of preparation for the scan, either withdrawal of thyroid hormone or rhTSH stimulation, will be evaluated. Seven days after administration of ^131^I a post-therapy scintigraphy is made, combined with SPECT/CT if available.

#### Follow-up phase

Six months after therapy both Tg and TSH levels will be determined after rhTSH administration. If the previous ^18^F-FDG PET/CT or the ^124^I PET/CT showed pathological uptake, that specific PET modality will be repeated. If both PET techniques were positive during the pre-therapy phase, both the ^18^F-FDG PET/CT and the ^124^I PET/CT will be repeated.

If another treatment modality, e.g. surgery, external beam radiotherapy or multikinase inhibitors, is indicated after the ^131^I therapy the data of this additional therapy will be collected as well. If a metastatic lesion is removed surgically the histopathological specimen will be collected for additional staining and reviewing by an expert endocrine pathologist.

### Additional protocol information

#### Histopathology thyroidectomy specimen

From every included subject original resection specimens of the thyroid will be collected and if possible additional staining will be done. All specimens will be reviewed and scored by an expert endocrine pathologist.

#### Histopathology biopsies

If one or more biopsies are acquired from the subjects between the pre-therapy and therapy phase they will be stored fresh-frozen and analyzed later.

#### Review panel

The local nuclear physician will assess all scans and, additionally, an expert review panel consisting of experienced nuclear physicians will assess every scan and every lesion individually as either positive or negative. Finally, the expert panel will discuss their disagreements to reach consensus on every scan and of every lesion in each scan.

### Sample size calculation

The power calculation is based on the (conservative) assumption that 40% of patients currently undergo a futile treatment. With approximately 50 evaluable patients per year in the Netherlands, we estimate we are able to include a minimum of 100 patients in 3 years. With a sample size of exactly 100 evaluable patients, a two-sided 95.0% confidence interval for a single proportion using the Pearson-Klopper method for constructing the confidence interval (exact binomial CI) will extend 10% from the observed proportion for an expected proportion of 40%.

### Recruitment and consent

The patients will be selected for potential participation by the endocrinologist. After consultation with on whether the patient is eligible the local principal investigator of the study the endocrinologist informs the patient. Informed consent is acquired at least a week later by the local principal investigator. See Additional file 1 for a list of participating centers.

### Withdrawal of individual subjects

Subjects of the study can leave the study at any time for any reason without any consequences. The investigator can decide to withdraw a subject from the study for urgent medical reasons. For every subject that decides to withdraw from the study a new subject will be included. In this way the number of subjects included will not be changed. If subjects withdraw from the study they will be offered regular follow-up.

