**Methods/Design:**

In a multicenter prospective observational cohort study the hypothesis that the combination of ^124^I and ^18^F-FDG PET/CT can avoid futile ^131^I treatments in patients planned for ‘blind’ therapy with ^131^I, is tested.

One hundred patients planned for ^131^I undergo both ^124^I and ^18^F-FDG PET/CT after rhTSH stimulation. Independent of the outcome of the scans, all patients will subsequently receive, after thyroid hormone withdrawal, the ^131^I therapy. The post ^131^I therapeutic scintigraphy is compared with the outcome of the ^124^I and ^18^F-FDG PET/CT in order to evaluate the diagnostic value of the combined PET modalities.

This study primary aims to reduce the number of futile ^131^I therapies. Secondary aims are the nationwide introduction of ^124^I PET/CT by a quality assurance and quality control (QA/QC) program, to correlate imaging outcome with histopathological features, to compare ^124^I PET/CT after rhTSH and after withdrawal of thyroid hormone, and to compare ^124^I and ^131^I dosimetry.

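### Replacing withdrawals regardless of phase can leave a primary sample selected on the PET result, with the loss hidden behind an unchanged number of patients

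*Protocol article*

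**What the plan says.** The section Withdrawal of individual subjects sets no limit on when a patient may leave: "Subjects of the study can leave the study at any time for any reason without any consequences". It then gives the replacement rule, "For every subject that decides to withdraw from the study a new subject will be included", and its purpose: "In this way the number of subjects included will not be changed". It does not separate leaving before PET, between PET and 131I, or after the post-therapy scan.

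The order of events is fixed elsewhere. Both PET scans come first. Then, "After the pre-therapy phase, subjects will start thyroid hormone withdrawal 4 weeks prior to ^131^I therapy". The post-therapy scintigraphy follows seven days after 131I (Therapy phase). The intention is complete verification: "Independent of the outcome of the scans, all patients will subsequently receive, after thyroid hormone withdrawal, the ^131^I therapy".

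PET results are in local hands before therapy. Under Review panel, "The local nuclear physician will assess all scans", and the section on the interval between the pre-therapy and therapy phases acts on positive findings: "If either the ^18^F-FDG PET/CT or the ^124^I PET/CT shows metastatic lesions and it is possible to acquire a biopsy from the lesion", a biopsy is taken.

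Study objectives defines a futile treatment by a negative post-therapy scan. Study endpoints makes the primary endpoint the number of futile treatments that PET could have avoided. Sample size calculation works with exactly 100 evaluable patients.

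**The concern.** A patient who leaves between PET and 131I has an index-test result but, unless a post-therapy scan made in routine care can be used, no reference standard. That patient cannot be classified as futile or not futile, so is not evaluable. Under the replacement rule another patient takes the place.

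The Background describes the burden of hormone withdrawal and the toxicity of 131I when it brings no benefit. A patient, or a treating physician, who knows that PET predicts no iodine uptake therefore has a plausible reason to stop. Such patients are mostly the ones the primary endpoint counts. Loss in the other direction is also conceivable, because PET-positive patients are the ones offered biopsy and may be steered to other treatment.

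At stake are the avoidable count, the futile share, sensitivity and specificity. The rule under Premature termination of the study is affected too: it counts patients with negative 124I PET and positive scintigraphy, and an unverified PET-negative patient can never enter that count.

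**Working it through.** **The protocol's own figure.** The exact (Clopper-Pearson) 95% interval for 40/100 is 30.3% to 50.3%, that is −9.7 and +10.3 points, half-width 9.97. The stated 10% reproduces. Without replacement the half-width would be 10.5 points for 36/90 and 11.2 for 32/80. Replacement thus protects precision only.

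**Inputs.** Futile share 40% (Sample size calculation). The document gives neither PET accuracy nor withdrawal rates; both are assumed below.

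**Definitions.** Sensitivity is the share of patients with a positive post-therapy scan for whom PET proposes 131I. Specificity is the share of futile treatments for which PET proposes no 131I, so it equals the share avoided. PET-negative means a proposal of no 131I.

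**Full verification, per 100, sensitivity and specificity 90%.** Positive scan: TP = 0.9 × 60 = 54, FN = 6. Negative scan: TN = 0.9 × 40 = 36, FP = 4. Avoidable treatments = TN = 36.

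**With loss.** Let a fraction w of PET-negatives and v of PET-positives leave after PET. The verified table is TN(1−w), FN(1−w), TP(1−v), FP(1−v), with sum S. After replacement to 100 evaluable patients, avoidable per 100 = 100 × TN(1−w)/S.

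| w | v | S | Avoidable per 100 | Futile share | Specificity | Sensitivity |
|---|---|---|---|---|---|---|
| 0 | 0 | 100 | 36.0 | 40.0% | 90.0% | 90.0% |
| 10% | 0 | 95.8 | 33.8 | 38.0% | 89.0% | 90.9% |
| 30% | 0 | 87.4 | 28.8 | 33.4% | 86.3% | 92.8% |
| 50% | 0 | 79.0 | 22.8 | 27.8% | 81.8% | 94.7% |
| 20% | 20% | 80.0 | 36.0 | 40.0% | 90.0% | 90.0% |
| 0 | 30% | 82.6 | 43.6 | 47.0% | 92.8% | 86.3% |

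Example, w = 30%: TN 25.2, FN 4.2, TP 54, FP 4, S = 87.4; 25.2/87.4 = 28.8 per 100; (25.2 + 4)/87.4 = 33.4%; 25.2/29.2 = 86.3%; 54/58.2 = 92.8%. The last row uses TP 37.8 and FP 2.8: 36/82.6 = 43.6 per 100.

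Predictive values do not move in any row: 36/42 = 85.7% for a negative proposal and 54/58 = 93.1% for a positive one.

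**Other accuracy assumptions.** Suppose PET flags 80% of futile and 5% of non-futile cases: TN 32, FN 3, FP 8, TP 57. With w = 30% and v = 5%, S = 22.4 + 2.1 + 7.6 + 54.15 = 86.25. Avoidable treatments fall from 32.0 to 22.4/86.25 = 26.0 per 100, and the futile share from 40.0% to 34.8%. With w = 0 and v = 20%, the count rises to 36.8.

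**Stopping rule.** The rule concerns 124I PET alone; the combined negative proposal is used here as a proxy. In the second scenario the discordant cases fall from 3.0 to 2.1/86.25 = 2.4 per 100, against a threshold of 3 patients.

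**Can it be repaired?** If loss depends only on the PET result, yes. At w = 30% in the first scenario, 25.2/29.4 = 85.7% of verified PET-negatives are futile; applied to all 42 PET-negatives this returns 36 per 100. Without that assumption, the 12.6 unverified patients give bounds of 25.2 to 25.2 + 12.6 = 37.8. At w = 10%, 4.2 are unverified and the bounds are 32.4 to 36.6. Each calculation needs the PET results of the patients who left.

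**The case against.** Several stronger readings are tempting, and the document does not support them.

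- *The plan discards withdrawn patients.* A reader might infer this from the replacement rule and the target of 100 evaluable patients. The rule fixes enrolment, not the analysis set, and an article may leave the analysis set to the full protocol or SAP. A completers-only analysis is therefore an inference.
- *Patients are told that PET is negative and so decline 131I.* No passage says this. The biopsy step shows action on positive scans only, and the stated intention is to treat everyone whatever PET shows. Leaving the study is also not the same as declining 131I.
- *The results are biased downward.* The direction depends on who leaves. It reverses if PET-positives leave more often and vanishes if loss is unrelated to PET.
- *Replacement causes the bias.* Missing verification causes it; without replacement the same bias would exist at a smaller number. Leaving before PET creates no partial verification, and leaving after the post-therapy scan leaves the primary endpoint observed.

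The 90%/90% scenario also fits poorly with the stopping rule. Six discordant cases per 100 would bring the third near patient 50 (3/0.06), so its figures are expected rates and not a forecast of a completed trial. The second scenario, with 3 per 100, is less exposed to this and shows a similar shift.

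These points limit the claim but do not remove it. The stated rule has no phase limit, and following it can produce a table selected on the index test with nothing in the number of patients to show it.

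**Conclusion.** The point holds as a conditional risk. If withdrawal between PET and 131I depends on the PET result, the avoidable count, futile share, sensitivity and specificity are biased, and replacement conceals this without correcting it.

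The size rests on assumed accuracy and loss rates. A 10% loss of PET-negatives costs about 2 avoidable treatments per 100 (36 to 33.8) and a 30% loss about 7 (36 to 28.8). At 30% the futile share shifts by 40.0 − 33.4 = 6.6 points, against a planned precision of 10 points. Predictive values are unaffected if loss depends only on PET. Selective loss of PET-negatives would also lower the count that feeds the stopping rule. The document supports neither a particular loss rate nor a direction.

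**What to change.** Amend Withdrawal of individual subjects, and the analysis plan to match:

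1. Treat only patients who withdraw before PET as simple replacements.
2. Do not replace in the primary analysis patients who leave after the post-therapy scan. Their endpoint is observed; use their data as consent allows.
3. Keep every patient with PET in the analysis set. Extra patients may still be enrolled for precision, but alongside those who left and not in their place.
4. Tabulate missing 131I or missing post-therapy scan by PET result and phase.
5. Report the primary proportion, sensitivity and specificity with a Begg-Greenes or inverse-probability correction, plus best-case and worst-case bounds. State the assumption behind the correction: loss depends only on the PET result and any recorded covariates used.

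Treatment of patients does not change. The cost is a short change to one section, one extra analysis and wider intervals. The widening is modest if few patients are unverified (32.4 to 36.6 per 100 at 10% loss of PET-negatives) and noticeable if many are (25.2 to 37.8 at 30%).
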